**Functional physical evaluation**

The **usual walking speed** will be assessed (Annex III). The distance to time ratio (m/s), measured over a space of 10 meters, will be used to evaluate the usual walking speed. Participants will be instructed to walk at a self-selected speed. The walking speed will be recorded only in the central 6 meters of the track identified laterally by tape marks, to avoid acceleration and deceleration bias. Participants will be instructed to stand with both feet behind the start line and start walking after the verbal command "*walk at your normal pace until the last mark on the ground, that is, as if you were walking on the street to make a purchase at the bakery"*; (Fritz 2009).

Another functional evaluation is the **Timed Up &Go (TUG**) test, which will be conducted according to the recommendations (Podsiadlo et al. 2009) (Annex IV). Participants will be seated in an armchair and will be asked to stand and walk for three meters, turn a cone, walk back, and sit on the chair. Participants will be encouraged to complete this walk as quickly as possible without running. The outcome will be the time taken to complete the task (Podsiadlo et al. 2009).

Additionally, the test will be performed using a chair without arms, with a height of 43.2 cm (Annex V). The chair will be placed against the wall to prevent displacement during the test. The test will begin with the participant sitting in the middle of the chair, back straight, feet approximately shoulder wide and resting on the floor at an angle slightly behind the knees, with one foot slightly in front of the other to help maintain balance when standing. The arms will be crossed against the chest. On receiving the "go" command, the participant will be asked to stand up (body upright and straight) and then return to the original sitting position. Participants will be encouraged to perform as many complete sit-up cycles as possible within a time limit of 30 seconds (Jones et al. 1999).

**Evaluation of strength of extensors of the knee:** Strength of the quadriceps muscles will be evaluated during the left and right knee extension, using the Microfet manual dynamometer (DMM) by means of isometric tests (Annex VI). The DMM is a reliable and valid assessment tool for measuring the muscle strength during knee extension in the elderly (Arnold 2010). With the participant sitting on a high chair, with the feet not touching the ground, the legs in a vertical position, and the dynamometer applied perpendicular to the leg proximal to the malleolus (Figure 1) and fixed by a strap to the chair, and the determination of the angulation of knee flexion will be performed with goniometer. The participant must push to extend the knee against the manual dynamometer. During the evaluation the verbal command will be given as "*stretch the knee by using greater force, stretch, stretch"*. This measure will be performed five times, and the highest and lowest force values recorded will be discarded. The average of the three remaining values will be calculated, and the isometric strength of the knee extensor muscles will be recorded in Newtons.

[figure not shown]

Figure 1. Patient positioning for evaluation of the extension force of the knee.

**Evaluation of muscle mass:** The body composition will be measured using the electrical bioimpedance apparatus *Biodynamics* tetrapolar, commonly described in the literature, which is a digital instrument, providing the values of resistance and reactance. The examination is performed by passing a low electric current (500 to 800 μA and 50 kHz) through the participant’s body, this imperceptible to the participant (Annex VII).

Compliance to the prior guidance given to participants will be verified before the examination. The guidelines require the patient to come to the test site on an empty stomach and not engage in physical activity until 12 hours before the test, not to consume alcohol for 48 hours before the test, and to empty the bladder 30 minutes before the test. The bioimpedance measurements will be obtained from the right side with the patient in a supine (lying down) position after removing the shoes and socks. The patient will be instructed to abduct the upper and lower limbs away from the body at approximately 30°, from the midline. The sites that will have contact with the electrodes will be cleaned with alcohol to ensure better contact with the electrode. The electrodes will be discarded after each measurement. The black cables (injectors) will be connected to the foot electrodes and the red cables (receivers) to the hand electrodes. “Alligator" connection clamps will be connected to the distal electrodes on the middle finger of the hand or near the toes. The red clamps will be placed on the proximal electrodes on the wrist and ankle. The detection electrode (red forceps) will be placed on the wrist on an imaginary line that divides the ulna and starts at the bony protuberance of the wrist; the black forceps electrode will be placed on the middle finger. On the foot, the electrodes will be placed on an imaginary line that divides the medial and lateral malleoli using the red forceps. The black forceps will be placed above the metatarsals of the toes (Figure 2).

The impedance, as opposed to the flow of running water, will be then measured. Before the examination, it will be checked whether the guidelines provided at the time of the interview have been complied with. Measures will be taken in the supine position after 15 minutes of rest. Using the resistance and reactance values obtained, the lean body mass (LBM) can be calculated using the equation: (LBM = total body water/0.732; being: total body water = 0.69 x height^2^ x resistance + 0.8). The lean BODYmass (kg) will be used to calculate the lean mass index (LMI), which is similar to the BMI, but uses the lean body mass (in kilogram)/height^2^ (in meters), to determine the muscle depletion (Pichard et *al*., 2000).

Figura 2. Illustration of the positioning of the electrodes during the bioimpedance evaluation.

**Evaluation of body mass and height:** The height of the subject expressed in centimeters (cm), will be measured in the orthostatic position after a deep inspiration, with both feet together and the weight of the body distributed on both feet. Stadiometer will be used to measure the height, and the values will be approximated to 0.5 cm. The body mass will be measured on a *Welmy®* mechanical anthropometric scale. This will be performed with the patients being barefoot and wearing light clothes, and will be expressed in kilogram (Kg).

**Social participation** will be assessed by the *Assessment of Life Habits* (*LIFE-H*) scale, which is divided into two sub-scales ("Daily Activities" and "Social Roles") that include twelve areas related to nutrition, fitness, personal care, communication, housing and mobility, responsibilities, interpersonal relationships, community life, education, work, and recreation. These categories correspond to the chapters of activity and participation component of the International Classification of Functioning, Disability and Health (ICF). Each item is scored according to the level of achievement and the type of assistance required to perform each activity; the scores range from zero (total restriction on participation) to nine (maximum participation). The following formula is used to obtain the score for each domain: (Σ scores*10)/(number of applicable items*9), and for the total score, the average score of each domain is considered. Due to the irrelevance of the categories "employment" and "education" for most elderly subjects, these will not be considered for the analysis; thus, there will be 10 categories and 59 items.

**Fear of falling** will be assessed by the International Falls-Efficacy Scale-Brazil (FES-I-BRAZIL) (Annex IX). The FES-I-Brazil is an adapted and validated scale for the Brazilian population that has adequate intra and inter-evaluator reliability. This questionnaire will be administered by the researcher physiotherapist trained for this evaluation, and will be conducted through an interview in a private and reserved environment. It comprises questions about 16 varied daily activities, from simple activities such as bathing, to activities that require a greater degree of independence, such as participation in social activities (Camargos et al, 2007). Each item has a score ranging from 1 to 4 points. A score of ≥ 23 is considered to be associated with sporadic fall history and ≥ 31 points is associated with recurrent fall.

**Intervention:** After the baseline evaluation and randomization, the participants will be submitted to one of the two muscle training modalities (electro-stimulation or resistance) for a period of eight weeks, as described below. For each training modality (electro-stimulation or resistance) a maximum of two participants will be allowed to undergo simultaneous training. Regardless of the training modality, two slots per week will be offered to each participant: Tuesdays and Thursdays or Mondays and Wednesdays during the morning or afternoon periods.

**Electro-stimulation group:** The participants assigned to this group will be submitted to whole-body electro-stimulation, which can simultaneously activate 8 to 12 muscle groups (upper legs, upper arms, abdomen, thorax, lower back, upper back, and large dorsal) with different intensity adjustments. This training will be performed in the Physical-Functional Performance Laboratory of the Faculty of Physical Therapy, UFJF, with up to two participants per session simultaneously. The bipolar electric current by MihaBodytec® devices (Gersthofen, Germany), will be initially applied with the following parameters: 85 Hz frequency, pulse amplitude of 350 𝜇s intermittently, with 6 seconds of stimulation to perform the movement and 4 seconds of rest (Table 1). The current intensity can be individually decided and modified during the electro-stimulation session. The applied protocol will be intermittent low intensity/low amplitude movement, based on the parameters described in other studies (Kemmler et al, 2014, 2013). Participants will be subjected to and supervised for 18 minutes of full body electrostimulation training, twice a week, for 8 weeks. The training sessions will be monitored by a trained physiotherapist, and with visual and acoustic stimuli guided by videos that exactly mimic the movements of the protocol. Based on previous studies, the WB-EMS protocol will follow the commercial WB-EMS settings with low load and narrow range of motion. It will involve five basic movements ("central exercises") shown in Table 1; these will be combined and slightly modified to generate 12 dynamic exercises that will be performed without any additional charge in a standing position. The training with WB-EMS will be structured in one to two series of 6 to 8 repetitions. The amplitude, speed, and corresponding intensity generated by the movement will be low (i.e. semi squat: flexion of the leg <35°) to avoid harmful effects of the exercise itself, but will be adequate to help muscle activation. In addition, no progressive increase related to exercise will be applied during the study. After the adaptation period of 4 WB-EMS sessions, the intensity of the current will be adjusted individually according to the participants' tolerance. Considering the difficulty of accuracy in prescribing the intensity of electro-stimulation due to regional differences, participants will be guided to maintain a perceived "strong" effort rate (Scale between "5 to 7" from 0-10) (Borg, 1990) during contraction. Current intensity is the key element for positive effects compared to the conventional exercise programs. The corresponding current intensity for each region of the body will be saved on the equipment chip to generate a fast, reliable, and valid setting during subsequent WB-EMS sessions.

Table 1.Concomitant movements during WB-EMS

1. Semi squat (6 s down) with arm extension/weight lifting (6 s up) with arm bending

2. Semi squat (6 s down) with trunk flexion (abs)

3. Semi squat (6 s down) with pulleys/semi squat (6 s up) with lifting

4. Semi squat (6 s down) with arm abduction (back)/semi squat (6 s up) with arm abduction (breast)

5. Semi squat (6 s down) and with rowing exercise (6 s up)

**Resistance training group:** The participants in this group will receive physical training in the weight training room of the Physical Education Faculty of UFJF. Each training session will include a 10-minute warm-up, including a walk and movement of different body segments: arms, wrists, fingers, shoulders, legs, and ankles. The resistance training will involve eight weeks of weight training (front puller, knee extender, straight supine, pulley, etc.) involving all major muscle groups. Participants in this resistance training group will be asked to attend two sessions per week for a period of 50 to 60 minutes each. Individual adaptations to the training protocol will be made regularly, according to individual performance. To define the training intensity, a load of 1-RM will be estimated. 1-RM has been widely used as the gold standard for checking the muscle strength. For the quantification of 1-RM, repeated attempts to obtain loads similar to the 1-RM test will be made (three to five attempts) with the same interval between the attempts (two to five minutes). The highest load performed by the participant, well positioned and without movement compensation, will be defined as 1-RM. The intensity will be based on the number of possible repetitions (week 1-2: fifteen repetitions, week 2-6: nine repetitions, with an intensity of 50-60% at 1-RM in the first two weeks, and then with 70-80% at 1-RM. Participants will be continuously asked about effort perception through Borg's symptom perception scale. In case of extreme fatigue, the intensity might be reduced or the session might be interrupted. A training volume of three series per exercise and 4 seconds between repetitions with 60 seconds rest between the series will be offered, and the participants will be encouraged to maintain muscle contraction for 6 seconds. Up to two participants might be trained simultaneously per session. This training will be accompanied by a physiotherapist and an experienced physical educator trained for the study protocol.

The duration of sessions of the two interventions will be different (18 minutes for the electro-stimulation group *vs*. 50-60 minutes for the resistance training group). This is because the whole-body electro-stimulation training stimulates simultaneous muscle contraction of several muscle groups and is therefore time-effective compared to the resistance training that works separately for each muscle group selected.

Table 2. Description of the phases of the study.

| Phase 1  Baseline assessment  -Gait speed  - Timed up and go  - Sit to stand test  - Maximal isometric knee extension  - Body composition  - Falls efficacy (FES-I)  - Social participation (Life-H) | RANDOMIZATION | Phase 2  Intervention  (8 weeks)  Electrostimulation    X  Resistance training | Phase 3  Post-intervention  -Gait speed  - Timed up and go  - Sit to stand test  - Maximal isometric knee extension  - Body composition  - Falls efficacy (FES-I)  - Social participation (Life-H) | Phase 4  Follow-up (Month 3 and 6)  -  -  -  -  -    - Falls efficacy (FES-I)  - Social participation (Life-H) |
| --- | --- | --- | --- | --- |

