**Primary outcome:**

Changes in muscle strength of extensors of the knee, walking speed, number of repetitions in the sit-leave test, and change in the lean mass in kilograms.

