**Financial budget:**

Material to be purchased with the researcher's own resources:

The necessary research instrumentation will be acquired through the release of the project resources approved in the Universal Call for Proposals FAPEMIG APQ-03054-17:

| **Item identification** | **Quantity** | **Capital**  **Value in Reais (R$)** |
| --- | --- | --- |
| 01 | **Full body electrostimulator**  **Brand:** Mihabodytec® **Function:** Simultaneous activation of muscle groups | 47.000,00 |

Instrumentation available at the Physical-Functional Performance Evaluation Laboratory of the Physical Therapy School of the UFJF:

| **Item identification** | **Quantity** | **Capital**  **Value in Reais (R$)** |
| --- | --- | --- |
| 01 | **Manual Dynamometer**  **Brand:** MircrofetFunction**:** muscle strength evaluation | 3.000,00 |
| 01 | **Electrical Bioimpedance**  **QUANTUM II - Brand**: RJL Systems, Inc. (USA) **Function**: evaluation of body composition | 11.800,00 |

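### The lean-mass equation multiplies height squared by resistance and gives no height unit; applied as written, a primary outcome takes impossible values and moves in the wrong direction

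*Protocol*

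**What the plan says.** Under Evaluation of muscle mass (in Procedures and Instruments), the protocol describes a tetrapolar bioimpedance device "providing the values of resistance and reactance". It is not said to report lean mass itself. The step from readings to kilograms is introduced by "Using the resistance and reactance values obtained, the lean body mass (LBM) can be calculated using the equation" and has two parts: "LBM = total body water/0.732", and "total body water = 0.69 x height^2^ x resistance + 0.8".

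The same lean body mass is then divided by height squared, in metres, to give the lean mass index. No unit for height or resistance appears inside the total body water equation. Under Evaluation of body mass and height, height is recorded in centimetres.

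The Primary outcome section lists "change in the lean mass in kilograms" among the primary outcomes. No other section gives a second equation or corrects this one.

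On the device, Evaluation of muscle mass names "the electrical bioimpedance apparatus *Biodynamics* tetrapolar", while the Financial budget lists a Quantum II from RJL Systems as the bioimpedance unit available in the laboratory.

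**The concern.** In a bioimpedance equation of this kind, resistance should stand in the denominator. For a uniform conductor of length L, cross-section A and resistivity rho, R = rho x L / A, so volume = A x L = rho x L^2 / R. The more conducting water and lean tissue there is at a given height, the lower the resistance. The written equation has the opposite dependence.

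Two consequences follow if it is applied literally. The level of lean mass is physically impossible. And because height barely changes over eight weeks, the change in lean mass becomes a positive constant times the change in resistance, so each participant's change takes the wrong sign. The comparison between arms on this primary outcome would be read backwards, and the lean mass index would inherit both faults.

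The missing unit matters separately. The protocol records height in centimetres but uses metres for the index, and the equation's result depends heavily on which is entered.

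**Working it through.** **Inputs from the protocol.** Constants 0.69, 0.8 and 0.732 (Evaluation of muscle mass); height recorded in cm (Evaluation of body mass and height). There is no worked value in the protocol to reproduce.

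**Assumed inputs, not in the protocol.** Height 150-180 cm; resistance 400-600 ohm.

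**Formulas.**
- As written: LBM = (0.69 x h^2 x R + 0.8) / 0.732
- With division: LBM = (0.69 x h^2 / R + 0.8) / 0.732

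**Levels.** Lean body mass in kg:

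| Height | R (ohm) | As written, h in m | As written, h in cm | Divided, h in cm | Divided, h in m |
|---|---|---|---|---|---|
| 150 cm | 400 | 849.5 | 8,483,608 | 54.1 | 1.098 |
| 150 cm | 600 | 1,273.6 | 12,725,411 | 36.4 | 1.096 |
| 160 cm | 500 | 1,207.7 | 12,065,575 | 49.4 | 1.098 |
| 180 cm | 400 | 1,222.7 | 12,216,395 | 77.4 | 1.101 |
| 180 cm | 600 | 1,833.6 | 18,324,591 | 52.0 | 1.098 |

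The extremes written out:
- As written, metres, lowest: (0.69 x 1.50^2 x 400 + 0.8) / 0.732 = 621.8 / 0.732 = 849.5 kg.
- As written, metres, highest: (0.69 x 1.80^2 x 600 + 0.8) / 0.732 = 1,342.16 / 0.732 = 1,833.6 kg.
- Divided, cm, lowest: (0.69 x 150^2 / 600 + 0.8) / 0.732 = 26.675 / 0.732 = 36.4 kg.
- Divided, cm, highest: (0.69 x 180^2 / 400 + 0.8) / 0.732 = 56.69 / 0.732 = 77.4 kg.

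The conclusion does not depend on the assumed resistances. For the written equation to return even 80 kg at 1.60 m, R would have to be (80 x 0.732 - 0.8) / (0.69 x 2.56) = 57.76 / 1.7664 = 32.7 ohm.

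**Lean mass index** at 160 cm and 500 ohm: about 472 kg/m^2 as written with height in metres (1,207.7 / 2.56), against 19.3 kg/m^2 with division in cm (49.4 / 2.56).

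**Direction.** Take a 160 cm person whose resistance falls by 3%, from 550 to 533.5 ohm.
- As written, metres: (971.52 + 0.8) / 0.732 = 1,328.3 kg becomes (942.37 + 0.8) / 0.732 = 1,288.5 kg, a change of about -40 kg.
- Divided, cm: (17,664 / 550 + 0.8) / 0.732 = 44.97 kg becomes (17,664 / 533.5 + 0.8) / 0.732 = 46.33 kg, a change of about +1.4 kg.

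**Unit.** The last column of the table shows that changing the operator alone is not enough. With division and height in metres, 0.69 x h^2 / R is below 0.006 throughout, and everyone scores about 0.8 / 0.732 = 1.1 kg.

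**The case against.** The best defence is that this is a transcription slip that would correct itself. Lean masses of a tonne or more would be obvious at the first participant, and the Sample Size section plans a pilot of 10 subjects. The device supplies raw resistance, so if the readings are kept, lean mass can be recomputed. The wording that introduces the equation is also permissive. Most of this stands. A reader might infer that the trial would report a reversed lean-mass result. The protocol does not support so strong a reading, because someone would have to analyse and publish absurd values unnoticed. What remains is that no other equation is offered. The operator and unit for a primary outcome would then be chosen after data exist.

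Could the multiplication sign come from reading the PDF? That is unlikely: the division slash before 0.732 survives in the same sentence, and the disputed operator is a printed character, not a gap.

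Three other inferences go too far.
- *Lean mass always comes out above some fixed figure, such as 1,200 kg.* That depends on the assumed heights and resistances and on metres. At 1.50 m and 400 ohm the result is about 850 kg.
- *The division form is established as the right equation.* The document shows that the written form cannot be right; it does not show which form is. The equation carries no citation of its own (the reference-values study cited nearby follows the lean mass index). The introducing sentence also mentions reactance, which neither form contains, so the operator may not be the only discrepancy.
- *Two devices would be used across visits and shift the change scores.* The protocol names two makes in two sections, but nothing says that both will be used or that they will be switched.

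**Conclusion.** The point holds. The equation for a primary outcome is wrong as printed, nothing in the protocol corrects it, and it leaves the height unit open.

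The size is about 850-1,830 kg in metres and 8.5-18.3 million kg in centimetres. These figures rest on assumed heights of 150-180 cm and resistances of 400-600 ohm. The impossibility of the values does not hinge on that choice. The reversed direction needs no assumed values; it follows from the form of the equation.

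The harm is conditional on the formula being applied literally. The likelier course is an unplanned correction during analysis, which is still a poor way to settle how a primary outcome is calculated. The difference in device names is a minor inconsistency and adds nothing to the weight of this point.

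**What to change.** Check the total body water equation against its source and correct it before it is used. The probable form is 0.69 x height^2 (cm) / resistance (ohm) + 0.8, but the source must decide, including whether reactance enters. Give its citation next to it.

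State the units of height and resistance inside the equation, and keep them distinct from the metres used for the lean mass index. Store raw height, resistance and reactance for each visit so that the derived value can be recomputed. If any lean mass has already been calculated, recompute it from those readings and record the correction.

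As a minor matter, reconcile the bioimpedance device named under Evaluation of muscle mass with the one in the Financial budget.

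The cost is one line in the protocol and in the calculation sheet, plus a look at the source. Nothing changes for participants.
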